#### Pathology

This study would not influence current pathological examination.

After the placement of wire markers on the fresh specimen, the specimen is sent together with the sentinel node immediately to the pathologist. The pathological examination of the surgical specimen and sentinel node is as follows:

The three dimensions of the surgical specimen are measured macroscopically. Specimens will be carefully inked and cut in 4-mm slices. Subsequently, the tumour diameter, the site of the tumour in the surgical specimen, the margin status and the smallest distance to the tumour-free resection margin will be measured (mm). The margin status and the smallest distance to the tumour-free resection margin will be measured more precisely using microscopy (mm), and finally, tumour characteristics (e.g. tumour differentiation, receptor status) will be recorded. The three dimensions of the sentinel node are measured macroscopically. Lymph nodes measuring < 5 mm are examined in toto, nodes measuring > 5 mm are cut. Microscopically the presence and size of metastasis are defined (mm).

### Calculations

The ratio of the resected volume to the optimal resected volume can be calculated from the diameter of the tumour and the three dimensions of the specimen.

Three assumptions are made:

1) the tumour is spherical (using the radius (= ½ diameter),

2) in an optimal resection volume, a margin of 1 cm is excised around the tumour and

3) the excised specimen is ellipsoid.

The volume of the excised specimen will be measured during surgery by fluid displacement and the histopathological ellipsoid calculation will serve as a control.

- The volume of the tumour will be calculated by 4/3πr ^3^.

- The optimal volume required for excision will be calculated by adding a resection margin of 1 cm to the lesion radius and converting this value into a spherical volume using the formula 4/3π(r + 1 cm) ^3^.

- The volume of the surgical specimen will be calculated using the formula 4/3πa b c (with a, b and c as given in the pathology report). The specimen volume will be compared with the optimal excision volume, resulting in a ratio (Figure 6) [29].

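### The ellipsoid formula for specimen volume needs semi-axes but is given the pathology dimensions, so the control volume, and any ratio built from it, is 8 times too large

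*Protocol article*

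**What the plan says.** All of this is in the protocol article.

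- **Calculations, specimen formula.** The specimen volume "will be calculated using the formula 4/3πa b c (with a, b and c as given in the pathology report"). The shape assumption behind it is that "the excised specimen is ellipsoid".
- **Pathology, what is measured.** "The three dimensions of the surgical specimen are measured macroscopically". The section does not mention half-lengths or semi-axes.
- **Calculations, tumour.** Here the halving is explicit: "the tumour is spherical (using the radius (= ½ diameter").
- **Calculations, optimal volume.** The denominator of the ratio is obtained by adding the 1 cm margin to the tumour radius and "converting this value into a spherical volume using the formula 4/3π(r + 1 cm) ^3".
- **Calculations, ratio.** The section opens by saying that the ratio "can be calculated from the diameter of the tumour and the three dimensions of the specimen". It closes by comparing specimen volume with optimal volume, directly after the ellipsoid formula.
- **Calculations, rank of the two volumes.** "The volume of the excised specimen will be measured during surgery by fluid displacement and the histopathological ellipsoid calculation will serve as a control". Perioperative parameters also describes the displacement measurement.
- **Sample size calculation.** Resected volume is the primary endpoint, and harmful excess is defined by a ratio above 1.0 together with a volume above 85 cm³.

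**The concern.** An ellipsoid has volume 4/3π times the product of its three semi-axes. Specimen dimensions measured macroscopically are ordinarily full length, width and height. If those go into the formula unhalved, each of the three factors is doubled. The section halves the diameter for the tumour but says nothing of the kind for the specimen, so numerator and denominator of the ratio would be on different scales and the error would not cancel.

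Two uses are at stake. The ellipsoid volume is the control for fluid displacement, and an eightfold error makes that control useless. The thresholds of 1.0 for the ratio and 85 cm³ for volume are absolute, so they lose their meaning for any value taken from the formula as written.

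A related gap is that the section ranks displacement as the measurement but describes the ratio in terms of the three specimen dimensions. It therefore does not settle which volume is the ratio's numerator, and that decides whether the error reaches the ratio.

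**Working it through.** **Inputs.** Specimen formula, optimal-volume formula and 1 cm margin: Calculations. Three specimen dimensions: Pathology. Worked optimal volume of 33.51 cm³ for a 2 cm tumour, and 244/726 specimens above 85 cm³ in the retrospective series: Background. Thresholds: Sample size calculation.

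**Step 1: reproduce the plan's own figure.** With tumour radius r = 1 cm and a 1 cm margin, 4/3·π·(1 + 1)³ = 33.51 cm³. This matches the Background, so the denominator is correctly based on the radius.

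**Step 2: the general factor.** With full dimensions a, b and c, the ellipsoid volume is 4/3·π·(a/2)(b/2)(c/2) = π/6·abc. The formula as written gives 4/3·π·abc. The quotient is (4/3)/(1/6) = 8, whatever the shape. The literal result is also 4/3·π = 4.19 times the enclosing box a·b·c, which is impossible for a body inside that box.

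**Step 3: examples for a 2 cm tumour (optimal volume 33.51 cm³).**

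| Specimen (full dimensions) | π/6·abc | Ratio | 4/3·π·abc as written | Ratio |
|---|---|---|---|---|
| 4 × 4 × 4 cm (ideal) | 33.51 cm³ | 1.00 | 268.08 cm³ | 8.00 |
| 5 × 4 × 3 cm | 31.42 cm³ | 0.94 | 251.33 cm³ | 7.50 |

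**Step 4: the 85 cm³ threshold.**
- Correct formula: 85 cm³ is reached when abc = 85/(π/6) = 162.3 cm³, a geometric mean dimension of 5.46 cm.
- As written: it is reached when abc = 85/(4/3·π) = 20.29 cm³, a geometric mean dimension of 2.73 cm and a true volume of 85/8 = 10.6 cm³.
- An ideal excision measures the tumour diameter plus 2 cm, so as written it passes 85 cm³ once the tumour exceeds 2.73 − 2 = 0.73 cm. For a 1 cm tumour the true ideal volume is 14.14 cm³ and the formula as written gives 113.10 cm³.

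**Step 5: plausibility against the retrospective series.** There, volumes were derived from pathology reports and 244/726 = 33.6% exceeded 85 cm³. Had full dimensions been used unhalved, the other 66.4% would have had true volumes of at most 10.6 cm³, which is below the ideal volume for even a 1 cm tumour. So half-dimensions were probably used in that series, although the article does not print its formula.

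**Step 6: what a constant factor does.** Multiplying every ratio by 8 in both arms leaves a t-test and the relative difference between arms unchanged. It multiplies an absolute difference and its confidence limits by 8, and it changes every classification against a fixed cut-off that a value crosses when multiplied by 8.

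**The case against.** The strongest reply is that the trial does not depend on this formula. Resected volume is measured in theatre, and the plan says it "will be measured during surgery by fluid displacement and the histopathological ellipsoid calculation will serve as a control". The 85 cm³ cut-off can be applied to displacement volumes without any ellipsoid. This stands: the primary volume endpoint and the sample size are untouched.

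Second, the formula is the right one for an ellipsoid, its symbols are not defined in the text, and Figure 6, which illustrates the comparison, is not shown. It may label a, b and c as semi-axes, and the retrospective 33.6% suggests halving in practice. This limits the certainty: the defect lies in the rule as written, and an error in the trial's computed data is not shown. It does not remove the point, because the text says to use the values as reported and states a halving only for the tumour.

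Third, an eightfold disagreement with displacement would show at the first specimen, and the recorded dimensions allow recalculation. That is true, and it makes the error recoverable. It is no reason to leave the rule uncorrected.

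A reader might go further and infer that nearly every patient in both arms would be classed as excessively resected and the trial's contrast lost. The documents do not support that. It would require the control volume to replace the displacement volume in the classification, and relative comparisons of a continuous ratio would survive even then.

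**Conclusion.** The point holds as an error in the stated formula with limited reach. On the reading that the pathology report gives full dimensions, the ellipsoid control volume is exactly 8 times too large, and so is any ratio calculated from the three dimensions. The factor does not depend on tumour size or specimen shape.

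Two things are invalidated: the agreement check between ellipsoid and displacement volumes, and any classification by ratio > 1.0 or volume > 85 cm³ that uses the ellipsoid volume. The displacement volume, the sample size and relative comparisons of continuous ratios are unaffected.

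The conclusion rests on two assumptions. One is that macroscopic dimensions are full lengths, which is the natural reading but is not spelled out. The other is that Figure 6 does not define the symbols differently. Whether the ratio itself is affected depends on its numerator, which the section leaves open.

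**What to change.** In Calculations, replace the specimen formula with V = π/6·a·b·c, where a, b and c are the full dimensions in cm from the pathology report. Equivalently, keep 4/3·π·abc and define a, b and c as half the reported dimensions. Check that Figure 6 uses the same definition.

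In the same place, state that the numerator of the ratio is the fluid-displacement volume and that the corrected ellipsoid volume is the control. Amend the opening sentence on how the ratio is calculated to agree.

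The cost is a few lines of text. No measurement, visit or sample-size figure changes, and any ellipsoid volume already computed from unhalved dimensions can be corrected by dividing by 8.

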**Figure 6 F6:**
[figure not shown]
**Comparing the specimen volume with the optimal excision volume**.

#### Postoperative

This study would not influence current postoperative treatment.

The current postoperative treatment is as follows:

Within two weeks after surgery, patients visit the outpatient clinic. Pathological results and further treatment (with multidisciplinary approach) are explained in detail. Complications are registered and treated, with special attention given to wound healing.

Approximately six weeks after surgery, all patients receive radiotherapy of the affected breast. Patients younger than 50 years old are treated with whole-breast irradiation (50 Gy in 25 fractions) including a simultaneously integrated boost (SIB), for a total dose of 68,75 Gy. Patients over 50 years old receive 40 Gy in 15 fractions with a SIB, for a total dose of 50,25 Gy. Radiotherapy strategies may vary slightly according to institutional guidelines.

If necessary, a medical oncologist is consulted for the administration of systemic therapy. Adjuvant therapy is administered according to national guidelines. When multiple axillary lymph node metastases are diagnosed, patients will receive adjuvant therapy prior to radiotherapy.

#### Cosmetic Analysis

During the follow-up visits three and six months after surgery, the cosmetic outcome will be evaluated. Standard 4-point view digital photographs, including the suprasternal notch, will be taken. These photographs will be scored by a panel consisting of six persons (including both professionals and non-professionals). The items scored will be the overall result, the appearance of the surgical scar, breast size, breast shape, nipple position and the shape of areola. The treated breast will be compared to the untreated breast, using the 4-point Lickert scale. Objective cosmetic analysis will be performed with the Breast Retraction Assessment (BRA) or comparable objective software. BRA values are calculated using measurements from the frontal view photographs and quantity the amount of retraction of the treated breast compared to the healthy contralateral breast by measuring nipple displacement. A large BRA value corresponds to increased asymmetry between the breasts and to poor cosmetic results (Figure 7). Subsequently, the patients' opinions concerning cosmetic outcome will be assessed using patient self-evaluation. Long-term follow-up (3 yrs) will probably be studied in a future research project.

**Figure 7 F7:**
[figure not shown]
**Breast Retraction Assessment**.

#### Quality of Life questionnaire

The EORTC QLQ-C30/-BR23 questionnaire will be completed by the patient prior to surgery and during follow-up visits three and six months after surgery. Using a personalised interview three and six months after surgery, patients' feelings concerning the cosmetic results of their breasts will be assessed more specifically. Results will be analysed over time.

### Follow-up

Oncological follow-up will continue according to national guidelines (every three months for the first two years). One year after surgery, follow-up will include no study issues. If the results of this study are promising, long-term results will be analysed (3 yrs of follow-up).

### Sample size calculation

The sample size was calculated based on the primary endpoint: volume of resected breast tissue. Previous studies have shown that excision volumes exceeding 85 cm^3 ^result in significantly higher cosmetic failure rates. In our recent retrospective multicentre study it was found that in 33.9% (244/726) of the patients the excision volumes exceeded 85 cm^3^. In 98.8% (241/244) of these patients, the CRR was > 1.0, implying that excess tissue was excised [20]. It can therefore be concluded that, in 33.2% (241/726) of all patients, excessive tissue resection resulted in impairment of the cosmetic outcome. Assuming that this excessive resection can be avoided with US-guided surgery, it is expected that only 10% of women will have excessive breast tissue resection (a ratio of > 1.0) that results in a worse cosmetic outcome (resection volume > 85 cm^3^). Therefore, we assume a difference in resected volume of 22.3% in favour of the US group. With a statistical power of 80% to detect this 22.3% improvement as significant (P < 0.05), we will require 57 patients in the palpation group and 57 patients in the US group. The margin status is currently involved in 22.5% of palpable breast tumour excisions. To improve this rate to 5%, we will require 60 patients in the palpation group and 60 patients in the US group. Therefore, the target sample size will be 120 patients.

### Timeline

The inclusion period will run from October 2010 to July 2011. The EORTC QLQ-C30/-BR23 questionnaire will be completed by the patient prior to surgery. Surgery will be scheduled 1-2 weeks after diagnosis. During a follow-up visit to the outpatient clinic, usually 1-2 weeks after discharge, complications will be recorded and treated. Three and six months after surgery, information will be collected from each patient concerning the cosmetic outcome and quality of life, and photographs will be taken. Patients can withdraw from the study at any time during the study period.

### Statistical analysis

Descriptive statistical methods will be applied. Statistical software (i.e. SPSS 15.0.) will be used for analysis. The 95% confidence intervals of the differences between the two groups will be calculated. The Chi-square test will be used for comparisons of dichotomous variables. The Students' t-test will be used, where appropriate, for comparisons of continuous variables. The Fisher's exact test will be performed where applicable. Multiple regression analysis will be used for comparisons of independent variables. The patient, tumour and treatment related differences will be calculated for the two treatment strategies.

An interim analysis will be performed after the inclusion of 60 patients (30 patients in each group). The final data analysis will be performed after the surgeries of the total of all 120 patients are completed. Definitive results are expected in December 2011.

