### Subjects and patient selection

One hundred and twenty patients will be recruited over a period of six months at a university medical center and several medium to large hospitals in the Netherlands. All women aged 25-75 yrs who are diagnosed with palpable early-stage (T1-2N0-1) invasive breast cancer in the trial centres will be invited to participate in this study. Breast cancer will be diagnosed with physical examination, mammography (2R) and US, and occasionally MRI of the breast and axilla. The diagnosis of invasive (ductal or lobular) breast cancer will be established with image-guided core needle biopsy or cytological puncture. All patients will be discussed in a multidisciplinary team, and suitable for BCT according to national guidelines. Participants will not have a history of prior mammary surgery of the affected breast, radiation therapy or neo-adjuvant therapy. Participants will have ASA Classification I-III and will be well-informed having signed an informed consent form.

Full ethical approval is obtained for this study from the Investigational Review Board of the VU University Medical Centre, including the Medical Ethical Review Board.

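### The stated trigger and December 2011 date for the final analysis come before the last 6-month cosmetic and quality-of-life visits that the stated inclusion period implies

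*Protocol article*

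**What the plan says.** The Statistical analysis section gives one trigger and one date. The trigger is "The final data analysis will be performed after the surgeries of the total of all 120 patients are completed"; the date is given as "Definitive results are expected in December 2011". Neither is limited to particular endpoints. The only later analysis mentioned is a conditional one at three years (Cosmetic Analysis; Follow-up).

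The Timeline section says "The inclusion period will run from October 2010 to July 2011" and "Surgery will be scheduled 1-2 weeks after diagnosis". It also says "Three and six months after surgery, information will be collected from each patient concerning the cosmetic outcome and quality of life". Two other sections confirm the visit schedule. Cosmetic Analysis has "During the follow-up visits three and six months after surgery, the cosmetic outcome will be evaluated", and Quality of Life questionnaire has "The EORTC QLQ-C30/-BR23 questionnaire will be completed by the patient prior to surgery and during follow-up visits three and six months after surgery".

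Subjects and patient selection gives a different recruitment length: "One hundred and twenty patients will be recruited over a period of six months".

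The Abstract lists cosmetic outcomes and quality of life as secondary endpoints. Sample size calculation names resected volume as the primary endpoint and also sizes the trial on margin status.

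**The concern.** The trigger suits outcomes known at or soon after surgery. It takes no account of outcomes that mature six months later, and the results date does not repair this, because under the Timeline the last 6-month visits fall after December 2011. A team that kept to the stated rule and date would report cosmetic outcome and quality of life without the 6-month value for the patients operated on last.

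Both outcomes are in the trial's title, and the closing section states an aim of showing superiority on them. The Quality of Life section also intends an analysis over time, for which the 6-month point is one of only two follow-up measurements. What is at stake is the completeness and precision of those comparisons, and clarity about which data set is the final one.

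**Working it through.** **Inputs**
- Inclusion: October 2010 to July 2011 (Timeline). No days are given, so the end is taken as 1 July or 31 July and the start as 1 or 31 October.
- Surgery: 7 to 14 days after diagnosis (Timeline), with inclusion dated from diagnosis (assumption).
- Last assessment: 6 months after surgery, every patient (Timeline; Cosmetic Analysis; Quality of Life questionnaire).
- N = 120; results in December 2011 (Statistical analysis).

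**Step 1: can the December date be reproduced from the Timeline?** Last visit = end of inclusion + 7 to 14 days + 6 months.
- Earliest: 1 July + 7 days = 8 July 2011; + 6 months = 8 January 2012.
- Latest: 31 July + 14 days = 14 August 2011; + 6 months = 14 February 2012.
- With no delay at all, surgery on 1 July 2011 gives 1 January 2012.

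No reading of the July end date completes the 6-month visits within 2011. This step needs no accrual assumption.

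**Step 2: the 3-month visits.** Last surgery + 3 months = 8 October to 14 November 2011. All are due before December.

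**Step 3: how many patients would lack the 6-month value?** The article gives no accrual curve; uniform accrual is assumed. With L the length of the inclusion window in days,

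number missing ≈ 120 × (days from the first surgery date whose 6-month visit is not yet reached, to the last surgery) / L, rounded down.

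Three windows were used: 1 October to 1 July (L = 273), 1 October to 31 July (L = 303) and 31 October to 31 July (L = 273), each with a delay of 7 or 14 days.

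| Data cut | Low case | High case |
|---|---|---|
| 31 December 2011 (surgery from 1 July on is too late) | 120 × 7/273 = 3 | 120 × 44/273 = 19 |
| 1 December 2011 (surgery after 1 June is too late) | 120 × 37/273 = 16 | 120 × 74/273 = 32 |
| Day of the last surgery (surgery in the last 181 days is too late) | 120 × 181/303 = 71 | 120 × 181/273 = 79 |

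As shares of 120 these are 3-16%, 13-27% and 59-66%. The shortest possible window, 31 October to 1 July (L = 243), leaves the December ranges unchanged but would raise the last row to 120 × 181/243 = 89.

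**Step 4: the other recruitment length.** Six months from October 2010 ends between 1 and 30 April 2011. The last surgery is then 8 April to 14 May, and the last 6-month visit 8 October to 14 November 2011. December 2011 is feasible. The surgery-based trigger would still be met six months before the last patient's final visit.

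**The case against.** The best defence is that the article says the analysis comes after the surgeries, which sets an earliest point and not a lock date. The next sentence expects results months later, and an expected date is a forecast, not a rule. The trigger also suits resected volume and margin status, the two outcomes that size the trial. No data collection is dropped, and a full protocol or SAP could hold staged analyses.

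Much of this stands. The primary endpoint and margins are untouched, and the 71-79 figure is a worst case, not the plan's stated intention. But a later cut within December 2011 still precedes the last visits under the Timeline. The point also does not rest on missing detail: a trigger, a date, a visit schedule and two recruitment lengths are all stated, and they do not fit together.

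Complete 3-month data soften the problem without removing it. Radiotherapy starts about six weeks after surgery and takes 15 or 25 fractions (Postoperative). At an assumed five fractions a week it ends around week 9 to 11, shortly before the 3-month visit, and the Background lists radiotherapy as a determinant of cosmetic outcome.

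Three stronger readings are tempting but unsupported:
- A reader might infer a data lock in mid-August 2011 with most 6-month data missing. The wording permits that but does not require it.
- A reader might infer that December 2011 works only with six months of recruitment. Inclusion to 31 May 2011 with surgery by 14 June gives a last visit on 14 December 2011, so about eight months would also fit, though with little time left for panel scoring.
- A reader might infer that arm-level results would reach unblinded patients and centres while self-evaluations continue. The article says nothing about blinding of patients or about release of results during follow-up.

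**Conclusion.** The point holds at moderate severity, for the secondary endpoints only. Under the Timeline the last 6-month visit falls between about 8 January and 14 February 2012, so definitive results in December 2011 cannot include complete 6-month cosmetic and quality-of-life data. The trigger contains nothing that would make the analysis wait for them. The two recruitment lengths contradict each other, and whether December is feasible depends on which one applies.

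The dates rest only on the article's own figures and on counting inclusion from diagnosis. The patient counts rest in addition on uniform accrual; slow or late-starting recruitment would push more patients past the cut. Because the missing values would be set by calendar time, and randomisation is stratified by institute, the loss should be roughly similar in the two arms. The main harm is therefore lost precision and an unclear data lock, not an obvious bias. The sample size and the analyses of volume and margins do not change.

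**What to change.** 1. In Statistical analysis, keep the trigger based on the last surgery, with its pathology report, for resected volume and margin status.
2. Tie the final analysis of cosmetic outcome and quality of life to the last patient's 6-month visit.
3. Make the recruitment period in Subjects and patient selection agree with the one in Timeline.
4. Move the definitive-results date for the secondary endpoints to after that last visit. Under the present Timeline this means January-February 2012 at the earliest, plus time for panel scoring and analysis.

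The cost is a change of wording and a secondary readout a few months later. No extra patients or visits are needed, and the primary results need not wait.
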